### Cluster randomized trial

We will conduct a two-arm cluster randomized trial comparing usual care and referral networks strengthened with an integrated HIT and peer support intervention. The primary outcome measure will be one-year change in SBP and a key secondary outcome will be change in CVD risk score. There will be a total of eight clusters in the trial, four in each arm, with each cluster in a geographically distinct referral network within the overall AMPATH CDM program. First, each referral network cluster will be stratified by size of the health facility at the secondary level. Then cluster randomization will be done within each strata. Cluster randomization will be done using a computerized random number generator in a 1:1 allocation sequence between intervention and control groups. One of the investigators, separate from other research or clinical staff, will generate the allocation sequence and complete randomization. Study staff will then enroll participants in the trial. The trial flow chart is shown in Fig. 4 and the SPIRIT figure is shown in Fig. 5. The SPIRIT checklist is provided in Additional file 1.

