### Outcomes

The primary outcome is one-year absolute mean change in SBP. The BP measurement for inclusion in the trial, and used in the primary outcome analysis, will be standardized and conducted by trained study staff. The key secondary clinical outcome is one-year change in overall CVD risk as measured by the QRISK2 score, which has been validated for calculating 10-year CVD event risk for Black Africans [58–66]. Treatment effect will be average change in SBP and QRISK2 score from baseline to month 12 and will be estimated using an intention-to-treat approach with appropriately specified regression models. Other clinical secondary outcomes will include mortality, hospital admissions, CVD complications, change in CVD risk factors and behaviors, and medication adherence [67]. The primary outcome and clinical secondary outcomes pertain to the individual participant level. We will also measure referral process metrics as key secondary implementation outcomes, including referral completion rates, median referral completion time, referral eligibility, referral indication, and referral appropriateness. Data will be collected on covariates we hypothesize may be related to our outcomes. These include patient demographics, socioeconomic and education status, clinical comorbidities, CVD risk factors, health behaviors, medication adherence, geographic location, referral level, provider level of training, and peer navigator and provider characteristics.

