### Analytical approach

We will use an analysis of covariance model with cluster effects to estimate and draw inference about treatment effects for both primary and key secondary outcomes. The model specification is:
$$ {\mathrm{y}}_{\mathrm{ij}}=\upalpha +{\upgamma}_{\mathrm{j}}+{\upbeta}_1{\mathrm{x}}_{\mathrm{ij}}+\uptheta {\mathrm{b}}_{\mathrm{ij}}+{\mathrm{e}}_{\mathrm{ij}} $$

where y_ij_ is SBP at the end of follow-up for the ith individual in the jth cluster, b_ij_ is baseline SBP, and the indicators x_ij_ represent intervention group membership, with usual care as the reference. Hence, β coefficient represents the difference in mean change in SBP between usual care and the intervention. The intercept is α and γ_j_ is the effect of the jth cluster. Cluster effects γ_j_ will initially be modeled as fixed effects, but we will use a mixed model structure and assign a normal distribution if the data support this assumption. We will compare key independent variables across the trial arms to ensure balance of the randomization process and adjust the model to estimate treatment effects as needed. For modeling QRISK2, we will use the transformation log(−log (QRISK2)) because the risk score ranges from 0% to 100% [73]. We will test the further hypotheses that changes in referral network characteristics and referral process metrics can mediate the effect of the intervention on CVD outcomes, and that baseline referral network characteristics can moderate the effect of the intervention on outcomes, by conducting a mediation and moderation analysis, respectively [74, 75]. Further details of the data management procedures and statistical methods, including approach to missing data, mediation and moderation analysis, and secondary outcomes, are available upon request from the authors.

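### Covariate adjustment of the primary SBP model depends on observed balance, and the written model omits the facility-size stratum used in randomisation

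*Protocol article*

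**What the plan says.** All references are to the protocol article.

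- **Design (Cluster randomized trial).** "There will be a total of eight clusters in the trial, four in each arm". Before allocation, "each referral network cluster will be stratified by size of the health facility at the secondary level". Allocation to arms is carried out inside those strata, whose number is not given.
- **Primary model (Analytical approach).** "We will use an analysis of covariance model with cluster effects to estimate and draw inference about treatment effects". The equation contains an intercept, a cluster effect, arm and baseline SBP. The definitions say that b "is baseline SBP, and the indicators x_ij_ represent intervention group membership, with usual care as the reference". No term for facility size or stratum appears.
- **Cluster effects (Analytical approach).** They "will initially be modeled as fixed effects, but we will use a mixed model structure and assign a normal distribution if the data support this", where the condition refers to normality.
- **Adjustment rule (Analytical approach).** Key variables will be compared "across the trial arms to ensure balance of the randomization process and adjust the model to estimate treatment effects as needed". The text gives no list of variables, no threshold for imbalance, and no statement of whether the adjusted or the unadjusted model is primary.

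**The concern.** There are two separate weaknesses, and neither causes the other.

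**The adjustment rule depends on the data.** A comparison of arms cannot secure balance; it can only describe what allocation produced. With four clusters on each side, sizeable differences in cluster-level characteristics are normal. A rule that adjusts when adjustment seems necessary, without saying for what or when, leaves several admissible primary models, and their estimates differ.

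**The stratum is missing from the written model.** Randomising within size strata balances size between arms. If size is related to the outcome, the estimate gains precision from that balance, but a model without size still counts size-related variation as error. The standard error is then too large, the test is conservative, and the precision bought by stratifying is partly given away.

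**Working it through.** **Inputs.** From Statistical power: SD 15, ICC 0.02 to 0.06, difference 10 mmHg, at least 200 per network, 15% loss (200 × 0.85 = 170 analysed), type I error 5% (taken as two-sided). From Cluster randomized trial: 8 clusters, k = 4 per arm. Assumed, because the article does not say: two strata of four clusters, with two per arm in each, except where stated.

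**1. The plan's own figures.** SE = SD·√(2·[1 + (m − 1)·ICC]/(k·m)), referred to a noncentral t with 2k − 2 df. Table 1 reproduces with k = 3, m = 200 and 4 df. For example, at ICC 0.04 SE = 15·√(2 × 8.96/600) = 2.59, noncentrality 10/2.59 = 3.86, power 81.8% (stated 82). Across ICC 0.02 to 0.06 the 10 mmHg row gives 96.5, 89.7, 81.8, 74.2 and 67.5% against 96, 89, 82, 74 and 67. Table 1 therefore matches the six networks named in that section. The eight-cluster design is used below; the mismatch is a separate matter.

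**2. How common is imbalance?** For a cluster-level covariate with SD 1, the difference between two means of four has SD √(1/4 + 1/4) = 0.707. P(|difference| > 1) = P(|Z| > 1.414) = 0.157. For at least one of five independent covariates this is 1 − 0.843⁵ ≈ 57%; for ten, about 82%.

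**3. How far can the estimate move?** Null simulation of eight cluster means (ICC 0.04, SD 15, m = 170; five assumed cluster-level covariates, one correlated 0.4 with the part of the between-cluster effect not due to the stratum). Adjusting for the most imbalanced covariate shifts the estimate by a median of about 1.0 mmHg. The six candidate models (unadjusted, or one covariate each) span a median of about 2 mmHg. The planned effect is 10 mmHg.

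**4. Leaving out the stratum, random cluster effects.** At ICC 0.04 the between-cluster variance is 0.04 × 225 = 9, and sampling variance of a cluster mean is 225 × 0.96/170 = 1.27. Let the stratum explain a share R of the 9.

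- True SE of the arm difference = √([9(1 − R) + 1.27]/2).
- SE that the model without stratum estimates ≈ √([9(1 − R) + 1.27 + 8 × 9R/6]/2), because the stratum sum of squares is spread over 6 df.

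| R | True SE | SE without stratum | Ratio | Type I error without | Type I error with |
|---|---|---|---|---|---|
| 0 | 2.27 | 2.27 | 1.00 | about 5% | about 5% |
| 30% | 1.95 | 2.36 | 1.21 | about 2% | about 5% |
| 60% | 1.56 | 2.46 | 1.57 | below 1% | about 5% |

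The type I error columns come from simulating the same eight-mean model.

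**5. Fixed cluster effects.** The eight cluster indicators have rank 8, and adding arm and stratum leaves it at 8. The indicators absorb the stratum, so its omission has no effect in that version. They absorb the arm as well, so the treatment effect is not estimable; that is a separate defect.

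**6. Cost of the size term.** k = 4, m = 170, ICC 0.06: design effect 1 + 169 × 0.06 = 11.14, SE = 15·√(2 × 11.14/680) = 2.72, noncentrality 3.68. No credit is taken for variance explained.

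| Size in the model | Cluster df | Power at 10 mmHg |
|---|---|---|
| None | 6 | 86% |
| One term (or two strata) | 5 | 83% |
| Separate terms for four strata | 3 | 69% |

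**The case against.** **The article is a condensed protocol.** Covariate lists usually sit in the full protocol or analysis plan, and the article offers further statistical detail on request. This stands as far as a missing list goes. It does not cover what the article does state: an explicit model without the stratum, and a rule that makes adjustment depend on observed balance.

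**The rule need not inflate type I error.** This also stands. In the simulation, mechanically adjusting for the most imbalanced covariate kept type I error at about 2 to 5%. It rose to about 9 to 13.5% with five covariates (stratum explaining 30% or none of the between-cluster variance) only if the most favourable model was picked and reported. A reader might infer that the model will be chosen with outcomes in view. The article does not propose that, and baseline comparisons can be made before any 12-month SBP exists.

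**A reader might infer adjustment for unsuitable variables.** The Outcomes section lists "medication adherence, geographic location, referral level, provider level of training, and peer navigator and provider characteristics" among the covariates to be collected. It does not call them adjustment variables for the SBP model. A check of randomisation balance points to baseline values, and peer-navigator characteristics have no counterpart in usual care to compare. The article does not support a claim that it would adjust for post-baseline adherence or navigator characteristics.

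**A reader might assume significance tests that ignore clustering.** The article says only that variables will be compared. No test or threshold is given, so no false-flag rate can be attributed to it.

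**Conclusion.** The concern holds in two limited parts. First, the as-needed clause leaves the primary estimate open to choice in a trial where chance imbalance is expected; under the assumed settings that choice is worth a median of 1 to 2 mmHg. The harm is an unsettled estimate, not automatic inflation of type I error. Second, with random cluster effects, leaving out facility size makes the analysis conservative to the extent that size explains between-cluster variance: the SE is about 21% too large at 30% explained and 57% too large at 60%. The omission is not itself a post hoc choice, and it costs nothing if size is unrelated to SBP change.

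The results rest on two strata of four clusters, ICC 0.04 for the error rates, and assumed covariate correlations. The article gives neither the number of strata nor the share of variance that size explains. The plan should be changed, but this does not by itself invalidate the trial.

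**What to change.** Replace the as-needed sentence with a primary model fixed in advance:

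- arm, baseline SBP, a random cluster effect, and facility size as one cluster-level term;
- at most a few baseline individual-level covariates, named before outcome data are seen (the choice is the sponsor's);
- baseline balance reported descriptively;
- any further adjustment labelled as sensitivity analysis and limited to baseline values.

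State the number of strata. Size should enter as a single term: separate terms for four strata would leave 3 df and about 69% power at ICC 0.06 before any credit for variance explained. With more than two strata, a single term recovers only the part of the stratum effect that follows the chosen scale, so some conservatism may remain.

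The change is to wording only. Its statistical price is one of the six cluster degrees of freedom, which takes power from 86% to 83% at 10 mmHg, SD 15, ICC 0.06 and 170 per cluster if size explains nothing.

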### Cost-effectiveness analysis

We will evaluate the incremental cost-effectiveness of HIT and peer support in terms of costs per unit change in SBP, per percentage change in CVD risk score, and per DALY saved. For each intervention arm, costs and potential cost offsets from the societal and payer perspectives will be captured using previously validated cost questionnaires used in Kenya for hypertension trials [78–80]. Study participants will complete one costing instrument, capturing healthcare utilization and expenditures, work loss, and transportation costs. All measures of burden will be monetized and, if there are differences across arms, used to quantify cost offsets from intervention delivery. Research staff will complete an additional costing instrument in order to capture all relevant labor, materials, supplies, and contracted services costs for all intervention activities. Only net incremental costs, after removing sunk costs and after factoring in cost offsets, will be included as the numerator in the cost-effectiveness analysis as these are the relevant costs for decision makers. We will also identify which activities drive the overall costs, and how costs would change if specific activities are added or eliminated. Effectiveness in terms of SBP and CVD risk score will be defined as above. DALY improvements will be estimated using well-defined relationships between blood pressure reductions and CVD DALYs averted [81]. We will also conduct sensitivity analyses to gauge the influence of key assumptions on the resulting incremental cost-effectiveness ratio.

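### The log(−log) model for QRISK2 yields a coefficient that is neither the average change in score nor the percentage change the article promises, and its scale and direction are not stated

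*Protocol article*

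**What the plan says.** Three sections of the protocol article bear on this.

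- **Outcomes** names the variable: "The key secondary clinical outcome is one-year change in overall CVD risk as measured by the QRISK2 score". It then names the effect to be estimated: "Treatment effect will be average change in SBP and QRISK2 score from baseline to month 12".
- **Analytical approach** fixes one model for all of these endpoints: "We will use an analysis of covariance model with cluster effects to estimate and draw inference about treatment effects for both primary and key secondary". Its coefficient is explained for blood pressure only: "β coefficient represents the difference in mean change in SBP between usual care and the intervention". For QRISK2 it adds: "For modeling QRISK2, we will use the transformation log(−log (QRISK2)) because the risk score ranges from 0% to 100" per cent. It does not say whether the score is divided by 100, which direction is beneficial on the new scale, or how the coefficient becomes a change in risk.
- **Cost-effectiveness analysis** uses the result in "costs per unit change in SBP, per percentage change in CVD risk score, and per DALY saved", and says: "Effectiveness in terms of SBP and CVD risk score will be defined as above".

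**The concern.** The effect is defined on the natural scale of the risk score in two sections and modelled on a non-linear scale in a third, with nothing in the article connecting them. A coefficient on the log(−log) scale has no single translation into risk points, because the translation depends on the participant's starting risk.

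Two smaller ambiguities add to this. The reason given for the transformation is a range in percent, yet in those units the formula fails for nearly every score. In the units where it works, it reverses direction relative to SBP, which is analysed with the same model.

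At stake are the size and interpretation of the key secondary clinical result, and the denominator of one of the three cost-effectiveness ratios.

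**Working it through.** The article gives no numerical result for QRISK2, so there is no figure to reproduce. The inputs are the printed formula g(p) = log(−log(p)), the stated 0% to 100% range, and the effect measures quoted above. The risk levels used below are illustrative assumptions.

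**1. Domain, in percentage points.** At a score of 10, −log(10) = −2.30, and the outer logarithm does not exist. The same holds for every score above 1. At exactly 1, −log(1) = 0 and the outer logarithm is again undefined. Only scores strictly between 0 and 1 percentage point give a value.

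**2. Direction, as a proportion.** The function is defined strictly between 0 and 1 and decreases throughout:

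| Risk | g(p) |
|---|---|
| 5% | 1.097 |
| 10% | 0.834 |
| 20% | 0.476 |
| 30% | 0.186 |

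Lower risk gives a higher value. A beneficial coefficient is therefore positive for QRISK2 and negative for SBP.

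**3. What one coefficient means in risk.** If the coefficient is b, a risk p becomes p′ = exp(−exp(g(p) + b)), which equals p raised to the power exp(b). With b = 0.10, exp(b) = 1.105:

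| Starting risk | Change in points | Relative change (points ÷ starting risk) |
|---|---|---|
| 5% | −1.35 | −27% |
| 10% | −2.15 | −21.5% |
| 20% | −3.11 | −15.6% |
| 30% | −3.57 | −11.9% |

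The change in points varies 2.6-fold (3.57 ÷ 1.35). The relative change varies too, so the coefficient is not a percentage change on either reading of that phrase. In the other direction, a fixed fall of 2 points is +0.157 on the transformed scale at 5% risk but +0.063 at 20%.

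**4. The two scales can disagree in sign.** Take month-12 risks of 10% and 20% in usual care and 4% and 27% in the intervention arm, with equal baselines.

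- Raw means: (10 + 20)/2 = 15.0% and (4 + 27)/2 = 15.5%. The intervention arm is 0.5 points worse.
- Transformed means: (0.834 + 0.476)/2 = 0.655 in usual care. The intervention mean is 0.064 higher, which favours the intervention.
- Back-transformed means: 14.6% in usual care and 12.8% in the intervention arm.

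The example also shows that back-transforming an arm's mean does not recover its average risk: 14.6% against 15.0%, and 12.8% against 15.5%.

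**5. Would the complementary form settle it?** log(−log(1−p)) rises with risk: −2.970 at 5%, −2.250 at 10%, −1.500 at 20%. That restores the usual direction. A fixed 2-point fall, however, is −0.521 at 5% risk (from 5% to 3%) and −0.117 at 20% (from 20% to 18%), about a 4.4-fold spread. For the printed form the spread is 0.157/0.063, about 2.5-fold. The complementary form does not by itself give an average change in score.

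**The case against.** The strongest reply is that the article is condensed. Outcomes promises suitably specified regression models, and Analytical approach says further methods for secondary outcomes are available on request. Fitting on a transformed scale and then converting back is compatible with an average-change effect, and the unseen plan may describe it. The cost-effectiveness wording can also be read as pointing to the average change under Outcomes rather than to the raw coefficient. This much stands: the absence of a back-transformation step is not in itself the finding. What remains is that the article prints a formula, an effect measure and a cost-effectiveness unit that do not fit together as stated.

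Four stronger readings are tempting, and the documents do not support them.

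- *The analysis would fail to compute.* That follows only if whole percentage points are entered. 0% to 100% can equally be read as 0 to 1, where the formula works, and the stated reason (a bounded score) suits that reading.
- *The reversed sign makes the test wrong.* It does not. A two-sided test and its interval are unaffected, and the article never says that a negative QRISK2 coefficient is favourable. The hazard lies in interpretation.
- *A 1 minus term was dropped by mistake.* The article contains no complementary form and claims no hazard interpretation. The source cited for the transformation is not at hand. This is conjecture.
- *The result could not be reported in the promised units.* It could, from the printed transformation, with a proper standardisation step.

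**Conclusion.** The point holds as a conflict between stated passages. Outcomes and Cost-effectiveness analysis fix the QRISK2 effect as an average change in score and as a cost per percentage change. Analytical approach fixes a model whose coefficient is a difference in mean log(−log(risk)). One coefficient of +0.10 covers falls from 1.35 to 3.57 points between 5% and 30% risk, and in a constructed example the two scales point in opposite directions. The formulas are exact. The risk levels and the four-value example are assumed, so they show what can happen, not what is likely in this trial.

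The unstated units and the reversed direction are lesser matters that one sentence each would cure. The consequence is limited to the key secondary clinical outcome and one cost-effectiveness denominator. The primary SBP analysis is untouched. The point should be corrected but does not threaten the trial's main conclusion.

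**What to change.** 1. State that QRISK2 is entered as a proportion, with the same transformation for the month-12 outcome and the baseline covariate.
2. State which sign of the coefficient favours the intervention. With the printed form it is positive.
3. Report the treatment effect as a model-standardised mean difference in percentage points, with a confidence interval that respects the clustering. Predict each participant's risk under both arms, back-transform each prediction allowing for the residual distribution, average within arm and subtract. Do not back-transform the arm means.
4. Use that difference as the denominator of the cost-effectiveness ratio, and say there that the unit is percentage points.
5. The sponsor should check whether log(−log(1−QRISK2)) was intended. Adopting it would align the direction with SBP, but it is optional and does not replace step 3.

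The cost is a few sentences and a little extra programming. No data collection changes, and Trial status places enrolment after the date of this protocol version.

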### Process evaluation

We will use the Saunders Framework [41] to conduct a process evaluation of the integrated HIT and peer support intervention. This process evaluation will be undertaken in order to monitor program implementation and better understand the relationship between intervention components and health outcomes. The Saunders Framework provides a systematic approach for guiding the evaluation of key implementation process measures across the following domains: fidelity (quality), dose delivered (completeness), dose received (exposure and satisfaction), recruitment, reach (participation rate), and context. Mixed quantitative and qualitative methods will be used to collect data from study participants and clinical staff, as well as from study and clinical encounter forms. This process evaluation will generate both formative and summative data [76, 77].

A combination of quantitative and qualitative approaches will be taken, including observation forms, checklists, surveys, record review, focus group discussions, and semi-structured interviews. Study participants, clinical staff, and study and clinical encounter forms will be the sources of data. Descriptive statistics will be generated for quantitative data, and thematic content analysis will be performed for qualitative data. Formative data will be reported iteratively to the study team and staff throughout the trial, while summative data will be reported at the end of the trial.

